### Methods in analysis to handle protocol non-adherence and missing data {20c}

The ITT principle will guide the analysis, ensuring robustness and generalizability by including all participants in their originally assigned groups, regardless of adherence to the intervention protocol or study completion. This approach minimizes biases from deviations, dropouts, or non-compliance, enhancing real-world applicability [45].

Missing data will be addressed using maximum likelihood estimation within the LMM framework. This method leverages all available data points, preserving dataset integrity while accounting for randomness in missingness without requiring imputation [46]. Combining ITT with maximum likelihood estimation ensures a comprehensive and unbiased assessment of the intervention’s effects.

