### Sample size {14}

A sample size power analysis was performed using G*Power 3.1.9.7 [36] to ensure the study’s feasibility within its constraints and the available population of individuals with mild intellectual disabilities (MID) who abuse substances. The calculation was based on the primary hypothesis, which posits that participants receiving the Beat the Kick intervention will show greater improvement in autonomous motivation compared to those in the control group. The analysis assumed a between-group design with four measurement points: pre-treatment (T1), post-treatment (T2), and follow-ups at 1 month (T3) and 6 months (T4). An effect size of *f* = 0.25 (medium effect), a power of 80%, and a significance level of 5% (two-sided) were used, with default settings for the correlation among repeated measures (0.5) and the non-sphericity correction (ε = 1, assuming sphericity).

The power analysis indicated that a sample of 82 participants is required to detect the expected effect with 80% power. Given the elevated risk of dropout among individuals with MID and co-occurring substance use—estimated at approximately 40% based on previous studies—the recruitment target was increased to 138 participants.

This adjusted target accounts for anticipated attrition and ensures that a sufficient number of participants will complete the study to maintain statistical power. Although recruiting 138 individuals from this population poses logistical challenges, it is considered feasible through targeted recruitment strategies, including partnerships with care providers and the use of established professional networks. This adjusted recruitment plan acknowledges the inherent risks of higher dropout rates but ensures the robustness of the study’s findings and feasibility within its framework.

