## Assignment of interventions: allocation

### Sequence generation {16a}

The study uses a Zelen pre-randomization design. Participants are individually randomized 1:1 to Beat the Kick or care-as-usual (CAU) using a centralized, computer-generated sequence with permuted blocks of variable size, stratified by addiction type (alcohol vs. cannabis/other drugs) to maintain balance across strata. Randomization is not clustered; clients from the same team may be allocated to either arm.

To minimize provider contamination while preserving individual randomization, trainers are assigned exclusively to a single arm (intervention or CAU) and do not deliver care in the other arm during the trial. Trainer and site identifiers are recorded at allocation; trainer will be modeled as a random effect in mixed-effects analyses to account for provider-level clustering. Any unavoidable cross-coverage will be documented a priori and examined in sensitivity analyses.

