## Statistical methods

### Statistical methods for primary and secondary outcomes {20a}

Data analysis will be conducted using R version 4.5.0 or later [41], following standard procedures for descriptive and inferential analyses.

The primary objective of this RCT is to assess the effectiveness of the Beat the Kick intervention compared to CAU in enhancing autonomous motivation for substance abuse treatment among adults with MID. It is hypothesized that participants in the Beat the Kick group will exhibit greater improvement in autonomous motivation from pre-test to post-test compared to the CAU group, with an anticipated medium effect size.

Linear mixed models (LMM) will be employed to test this primary hypothesis using the lme4 package in R [42]. LMMs are particularly suited for repeated measures data, accommodating both fixed and random effects [42]. Models will include fixed effects for group (Beat the Kick vs CAU), time (T1–T4), and the group × time interaction (primary effect of interest), with random intercepts and random slopes for time at the participant level to capture individual trajectories. The randomization stratification variable “addiction type” (alcohol vs cannabis/other drugs) will be included as a fixed effect in all models to adjust for baseline heterogeneity between strata; exploratory interaction terms with group and time (e.g., group × time × addiction type) will be examined to assess effect modification [43]. Baseline outcome values will serve as covariates to control for initial differences, mitigating regression to the mean [44].

Analyses will primarily adhere to the intention-to-treat (ITT) principle, preserving the integrity of randomization and providing a conservative estimate of the intervention’s effectiveness [45]. This approach ensures that all participants are analyzed in their originally assigned groups, irrespective of adherence or dropout. Complementary per-protocol (PP) analyses will also be conducted for participants who completed the intervention as intended, providing additional insights. Missing data will be handled using maximum likelihood estimation, a robust method that assumes data are missing at random, leveraging all available information without requiring imputation [46].

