Potential confounders, such as living arrangements (e.g., 24-h supervised care, outpatient services, or home-based support) and prior substance use treatment exposure, will be incorporated as covariates. These factors are expected to influence engagement and outcomes by shaping daily routines, support systems, and environmental stability. Trainer effects, which may vary due to differences in style, experience, or engagement, will be modeled as a random effect to minimize potential bias. Additionally, to prevent carry-over effects, trainers will be exclusively assigned to the intervention group, ensuring that training specific to Beat the Kick does not unintentionally influence CAU.

The secondary objective is to evaluate the intervention’s effectiveness in reducing substance use among adults with MID. It is hypothesized that the experimental group will show a greater reduction in substance use levels compared to the CAU group at follow-up. LMMs for secondary outcomes will mirror the primary model, including addiction type as a fixed effect (with exploratory interactions), and will adjust for baseline substance use levels.

To accommodate the Zelen design’s pre-randomization process, analyses will carefully consider group allocation at the pre-randomization stage, ensuring that group comparisons accurately reflect the intervention’s true effect. Sensitivity analyses will assess the robustness of results, including tests with and without outliers. Missing data will be handled using full information maximum likelihood (FIML), a robust method that leverages all available data and is generally preferred regardless of the underlying missingness mechanism [47]. Although FIML does not eliminate all bias under not-missing-at-random (NMAR) conditions, it typically yields less biased results than listwise deletion. Conclusions drawn under NMAR will be interpreted with appropriate caution, and the plausibility of the missing at random (MAR) assumption will be evaluated in light of the observed data structure and auxiliary variables.

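### Maximum likelihood is named for the mixed models where REML with small-sample degrees of freedom would handle missing data equally well and hold the 5% level better (minor)

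*Protocol article*

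**What the plan says.** Section {20c} of the protocol article states: "Missing data will be addressed using maximum likelihood estimation within the LMM framework". Section {20a} has "Missing data will be handled using maximum likelihood estimation" and, further on, "Missing data will be handled using full information maximum likelihood (FIML"). A later paragraph of {20a} names maximum likelihood again, for incomplete data. The rationale is that every available observation is used under missing at random and no imputation is needed.

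The models are to be fitted with lme4. Their fixed effects are group, time, group by time (the effect of interest) and addiction type. Participants have random intercepts and slopes. Section {20a} also makes the baseline outcome a covariate and adds living arrangement and prior treatment. On providers, {16a} says "trainer will be modeled as a random effect in mixed-effects analyses to account for provider-level clustering".

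The sample size section {14} fixes the error rate: "a power of 80%, and a significance level of 5% (two-sided) were used". The article gives no test statistic, no degrees-of-freedom method and no number of trainers.

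**The concern.** In lme4, maximum likelihood and REML are alternative fits. Maximum likelihood makes no allowance for the fixed effects that have been estimated, so its variance components are biased downward. The bias is worst for a random effect with few levels, which trainer could be. Standard errors of the arm contrast then come out too small, and a test without a small-sample correction rejects more often than its nominal level.

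At stake are the 5% level in {14} and how far the trainer term protects against provider clustering. The rationale in the text does not call for maximum likelihood over REML, because both use the same observed data under the same missing-at-random assumption.

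**Working it through.** **1. The plan's own figures.** Inputs from {14}: f = 0.25, four measurements, correlation 0.5, two-sided 5%. For the between-groups repeated-measures test, λ = N·m·f²/(1 + (m − 1)ρ) = 82 × 4 × 0.0625/2.5 = 8.2. With 1 and 80 degrees of freedom the power is 80.8% (79.8% at N = 80), so 82 reproduces. For dropout, 82/0.6 = 136.7, hence 137, or 138 for equal arms.

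**2. Inflation that needs no trainer assumption.** Take a T2 score compared between arms. From {20a} the mean parameters are intercept, group, addiction type, baseline, living arrangement (three named settings, so two terms) and prior treatment, which makes 7; one further term makes 8. With p mean parameters and df = N − p, maximum likelihood divides the residual sum of squares by N instead of df. The size of a Wald z test is therefore P(|t_df| > 1.96·√(df/N)).

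| N | p | df/N | ML, Wald z | ML, likelihood ratio | ML, t reference | REML, z |
|---|---|---|---|---|---|---|
| 82 | 7 | 0.915 | 6.5% | 6.2% | 6.1% | 5.4% |
| 82 | 8 | 0.902 | 6.7% | 6.4% | 6.2% | 5.4% |
| 138 | 7 | 0.949 | 5.8% | 5.7% | 5.6% | 5.2% |
| 138 | 8 | 0.942 | 5.9% | 5.8% | 5.7% | 5.2% |

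For N = 82 and p = 7, for example, the cut-off is 1.96 × √(75/82) = 1.874 on 75 degrees of freedom. If only the two arm means count (p = 2), as in a plain comparison of change scores, Wald z gives 5.6% at 82 and 5.4% at 138.

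**3. T1 kept as an outcome, trainer as an intercept only.** A trainer intercept is common to all of a participant's visits and largely cancels from group by time. This model was simulated under no effect with assumed variance components (1,000 runs per setting, Monte Carlo standard error about 0.7 points), using a z test:

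| Setting | ML | REML |
|---|---|---|
| 138 randomized, 40% dropout, 3 trainers per arm | 5.3% | 5.2% |
| 138 randomized, 40% dropout, 6 trainers per arm | 4.9% | 4.7% |
| 82 complete, 3 trainers per arm | 6.1% | 5.7% |

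The ratio of ML to REML standard errors is about 0.99 throughout.

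**4. Trainer variance acting on the tested contrast.** This arises, for instance, if T1 is a covariate and T2 to T4 are the outcomes. The arm difference is then a comparison between trainers, who are nested in arm under {16a}. Assume k trainers per arm, m participants each, total N of 80 to 84, and unit variance split into trainer (ICC) and residual parts. The true standard error is √[(1 − ICC + m·ICC)·2/(km)]. ML divides the between-trainer sum of squares by 2k, and REML by 2k − 2; each falls back on the pooled variance when the between-trainer part is the smaller. The corrected test uses REML with t on 2k − 2 degrees of freedom (N − 2 in the fallback), an approximation to Satterthwaite. Power is for the effect that gives 80% with 41 per arm and no clustering, 2.80 × √(2/41) = 0.62 SD. Results are from 200,000 runs per setting at an assumed ICC of 0.05:

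| Trainers per arm | ML, z | REML, z | REML, small-sample df | Power, ML z | Power, corrected |
|---|---|---|---|---|---|
| 2 | 14.1% | 9.8% | 6.4% | 66% | 30% |
| 3 | 10.5% | 7.7% | 4.7% | 69% | 41% |
| 6 | 7.2% | 5.9% | 4.3% | 73% | 61% |
| 10 | 6.1% | 5.3% | 4.3% | 74% | 68% |

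For ICC 0.02, 0.05 and 0.10, ML with z gives 7.5%, 10.5% and 14.0% at 3 trainers per arm, and 5.5%, 6.1% and 6.8% at 10.

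**The case against.** The strongest reply is that each of these sentences is about missing data. None sets REML aside, and the test statistic and degrees of freedom are ordinary analysis-plan content. That stands in part: silence on degrees of freedom is no fault in an article. The words maximum likelihood and FIML are in the text, however, and a programmer following them literally would switch off lme4's REML default.

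A reader might infer that the trial has few trainers and that its 5% test therefore rejects far too often. The documents do not support this. They give no trainer count, only that the specialists come from six organizations, and in the model with T1 as an outcome and a trainer intercept the effect is negligible. The large figures need the baseline-as-covariate reading, which {20a} also allows, together with few trainers.

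A reader might also take 82 completers as the analysis sample. That is the required number before allowance for dropout; the analysis is intention-to-treat on all available data from 138 randomized participants.

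Nor is maximum likelihood the whole cause. At 3 trainers per arm and ICC 0.05, moving to REML with z removes 10.5 − 7.7 = 2.8 points, and the degrees-of-freedom correction removes a further 7.7 − 4.7 = 3.0.

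**Conclusion.** The point holds as a minor one. The estimator named is the less suitable of two that share the same missing-data property. Read literally, it makes the test mildly liberal: 5.8-5.9% at 138 and 6.5-6.7% at 82, given a Wald z test and 7 to 8 mean parameters. Anything larger is conditional on trainer variance reaching the tested contrast and on a trainer count and ICC that are assumptions here. A material failure of the 5% level is not shown for the model with T1 as an outcome and trainer as an intercept.

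**What to change.** In {20a} and {20c}, state that the linear mixed models are fitted by REML and that the arm contrast is tested with Kenward-Roger or Satterthwaite degrees of freedom, for example through pbkrtest or lmerTest with lme4. Leave the missing-at-random statement as it is.

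The cost is a few words and a fitting option, with no further data or participants. Intervals become slightly wider. If trainers are few and their variance reaches the contrast, they become materially wider and nominal power falls, from about 69% to 41% at 3 trainers per arm and ICC 0.05. Part of the 69% is bought with excess type I error.

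### Likelihood estimation in lme4 keeps participants with missing outcomes but drops those with a missing baseline covariate, so the claim to use all data and all participants is too broad

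*Protocol article*

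**What the plan says.** Four statements in the protocol article have to be read together.

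- **Software.** Section {20a}: "Linear mixed models (LMM) will be employed to test this primary hypothesis using the lme4 package in R".
- **Covariates.** Section {20a} enters the T1 score: "Baseline outcome values will serve as covariates to control for initial differences". It adds living arrangements and treatment history: "prior substance use treatment exposure, will be incorporated as covariates". The stratification factor, addiction type, "will be included as a fixed effect in all models to adjust for baseline heterogeneity between strata".
- **Missing data.** Section {20c} on maximum likelihood: "This method leverages all available data points, preserving dataset integrity while accounting for randomness in missingness without requiring imputation". Section {20a} describes the same approach under a second name: "Missing data will be handled using full information maximum likelihood (FIML), a robust method that leverages all available data". It adds that this is typically less biased than listwise deletion.
- **Analysis set.** Section {20c} describes intention-to-treat as "including all participants in their originally assigned groups, regardless of adherence to the intervention protocol or study completion". The footnote to Table 3 defines it as everyone randomised.

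No section says what happens to a participant whose T1 score or other covariate is missing.

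**The concern.** A mixed model fitted in lme4 maximises the likelihood of the outcomes given the covariates. Missing outcome rows are handled well: a participant who misses T3 and T4 still contributes T1 and T2. Missing covariates are outside that likelihood, and by default any row with a missing covariate is removed before fitting.

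The T1 score, living arrangements and prior treatment exposure are each constant within a person. One blank therefore removes the participant at every visit. Full information maximum likelihood that extends to covariates would need a model for the covariates, and lme4 does not fit one. The plan's mention of auxiliary variables does not change this, because there they serve to judge whether missing at random is plausible.

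At stake is whether randomised participants with observed primary outcomes leave the primary analysis although the text says they stay. Because the text also says that no imputation is needed, it gives the analyst no reason to prevent this.

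**Working it through.** **1. Does the deletion happen?** Data were simulated for 138 participants at 4 visits (552 rows). The T1 score was missing for 7 participants and living arrangement for 5 others; all 12 had T2–T4 outcomes. Models were fitted by maximum likelihood with lmer in R 4.3.3, default handling of missing values (na.omit), with a random intercept per participant.

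| Model | Participants | Rows |
|---|---|---|
| Group × time, no baseline covariates | 138 | 545 (552 − 7) |
| Plus T1 score and living arrangement, T1–T4 as outcome | 126 | 504 (126 × 4) |
| Plus T1 score and living arrangement, T2–T4 as outcome | 126 | 378 (126 × 3) |

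The first model loses only the 7 missing outcome rows and no participant. The other two lose all 12 participants.

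**2. Which covariates could be missing?**

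- Addiction type is needed to randomise, so it should be complete.
- The T1 score should rarely be missing in someone with follow-up data. Section {10} uses the TSRQ, AUDIT and DUDIT for eligibility, and {16b} and {16c} place baseline assessment before assignment.
- Living arrangement should seldom be unknown. Unstable housing is an exclusion in {10}, and {15} draws participants from the organisations' own caseloads.
- Prior treatment is to be documented at pre-treatment ({18a}). It remains the most plausible gap.

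**3. How many would be dropped?** The documents give no rate. Assume that two covariates are missing independently, each in a share q. The share dropped is 1 − (1 − q)²:

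- q = 2%: 1 − 0.98² = 4.0%
- q = 3%: 1 − 0.97² = 5.9%
- q = 5%: 1 − 0.95² = 9.8%

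If only prior treatment had gaps, the share dropped would be q itself, 2% to 5%.

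**4. The protocol's sample size, reproduced.** Inputs from {14}: f = 0.25, m = 4 visits, correlation 0.5, two-sided 5%, power 80%. For a between-group repeated-measures F test, the noncentrality is

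λ = f² · N · m / (1 + (m − 1) · 0.5) = 0.0625 · N · 4 / 2.5 = 0.1 · N,

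with 1 and N − 2 degrees of freedom. N = 80 gives 79.8% and N = 82 gives 80.8%, so the stated 82 reproduces. For 40% dropout, 82 / 0.6 = 136.7, hence 137, or 138 as an even number for 1:1 allocation.

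**5. Power after deletion, same formula.** Completers = 138 × (1 − share dropped) × 0.6.

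| Share dropped | Completers | Power |
|---|---|---|
| 0% | 82.8 | 81.1% |
| 2% | 81.1 | 80.3% |
| 5% | 78.7 | 79.1% |
| 10% | 74.5 | 76.8% |

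**The case against.** The other side has a good case on size.

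- **The trigger is rare by design.** As step 2 shows, the T1 score and housing are reviewed at screening, and treatment history is to be collected. This stands. A reader might give the T1 score the same missingness as the other two covariates and reach 5.9%, 8.7% or 14.3% dropped for q = 2%, 3% or 5%. The eligibility rules do not support that.
- **The power base is only a yardstick.** It counts completers, whereas partial completers also contribute under maximum likelihood. The protocol's formula also tests the group difference averaged over four visits, while the primary endpoint is the T2–T1 change. That mismatch is a separate matter and should not be counted here.
- **The wording is standard.** For missing outcomes, the main problem with 40% expected dropout, it is correct. A reader might infer that the plan adopts listwise deletion throughout, or that intention-to-treat fails as such. The documents say neither. The loss follows from a software default and only for participants with a missing covariate.
- **Covariate handling is often left to the analysis plan.** True, and silence alone would be no finding. But this text is not silent: it names the software and the covariates, says imputation is not required, and states a property that the combination lacks.

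A reader might also count people who decline after Zelen randomisation. Those with no data at all are lost under any mixed model and are not part of this point.

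**Conclusion.** The point holds as a misstatement of limited size. The all-data and all-participants statements are right for missing outcomes and wrong for any participant with a missing person-level covariate. The mechanism is confirmed in lme4. It rests on the package's default handling of missing values, which the protocol does not override.

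The size rests on an assumed rate. With two covariates each missing in 2% to 5%, about 4% to 10% of participants would be dropped. That costs roughly 2 percentage points of power at 5% dropped and 4 at 10%, and under 1 point at 2%. The effect is probably small.

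A reader might go further and infer bias between the arms. Section {26a} seeks consent to assessments after participants know their arm, whereas {16b} and {16c} put baseline before assignment. On the first reading, gaps in baseline items could differ by arm. The documents do not show that they would, so this is a reason to close the gap and not a demonstrated bias.

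**What to change.** In {20a} and {20c}:

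1. Limit the maximum-likelihood statement to missing outcomes. Do not apply the full-information label or the no-imputation remark to covariates.
2. State that missing baseline covariates will be filled by simple imputation blind to arm, for example the mean (counts and scores) or mode (categories) within the addiction-type stratum. The A/B-coded dataset in {17a} makes this feasible.
3. Report, by arm, how many participants had a filled covariate.

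The cost is a few sentences and a few lines of code, with no new data. The downside is slightly weaker covariate adjustment where values are filled.

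One related matter should be settled separately. Section {20a} uses T1 both as a covariate and as a level of time: "time (T1–T4), and the group × time interaction (primary effect of interest". If that were resolved by keeping T1 only as a response, a missing T1 score would no longer remove anyone, and only the other two covariates would need the imputation rule.
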